### Outcome Measures

The CTS symptoms severity scale is a validated 11-item questionnaire that mainly inquires about severity, frequency and duration of night and daytime pain and numbness or tingling [14,15]. The CTS score ranges from 1 (no symptoms) to 5 (most severe symptoms). The *Quick*DASH is a validated 11-item questionnaire that mainly inquires about difficulties in performing daily activities, yielding a score from 0 (no disability) to 100 (worst possible disability) [18]. The SF-6D is a validated health utility measure that is used to compare cost-effectiveness of different treatments and the value ranges from -0.11 (worst health) to 1.0 (perfect health) [19]. All AEs are recorded during 24 weeks. Duration of sick leave for employed patients is recorded.

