## Background

Carpal tunnel syndrome (CTS) is the most common peripheral compression neuropathy in the upper extremity with a prevalence of 3.7% in the adult general population [1]. The prevalence of persons who have moderate or severe CTS but have not sought care or been diagnosed correctly is almost 1% in the general population [2]. CTS of mild severity is commonly treated with wrist splint but for moderately severe symptoms surgical treatment is often required [3]. Carpal tunnel release is one of the most common surgical procedures; the annual incidence in a US population (2001-2005) was 134 per 100,000 [4]

Although carpal tunnel release has been shown to produce good outcomes regarding relief of symptoms caused by CTS [5], it has several disadvantages including surgery-related pain and hand weakness [6]. These are common problems and may last several months after surgery. Other less common complications include wound infection, chronic regional pain syndrome, and nerve injuries [7,8]. In addition, surgery is associated with direct costs as well as indirect costs related to work absence after surgery because the majority of patients require sick leave for a varying length of time depending on the degree of postoperative morbidity and the type of work [9]. The median time of work absence has been 4 weeks in several studies, with a proportion of patients having long-term work disability [9]. The economic impact of work absence following surgery for CTS can be substantial both for the patients and the society. Consequently avoiding sick leave would be an important advantage for nonsurgical treatment.

Although many alternatives to surgery have been proposed there is little evidence to support the efficacy of most of these treatments [10]. Steroid injection into or proximal to the carpal tunnel is widely practiced in the treatment of patients with idiopathic CTS particularly in the United States [11]. However, the evidence for its efficacy beyond one month has not been established in placebo-controlled trials. In a recent Cochrane review of local corticosteroid injection for CTS, the authors concluded that there was evidence supporting clinical improvement at one month compared to placebo but no significant improvement after 8 weeks compared to nonsteroidal anti-inflammatory drugs or wrist splint [12]. None of the studies reviewed involved a double-blind comparison with a follow-up of more than one month.

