### Evaluations

At baseline and the last follow-up (Table 2) median nerve conduction testing of both hands is performed. The measurements include median nerve motor distal latency and sensory conduction velocity across the carpal tunnel, median nerve index finger-wrist sensory latency, or ring finger-wrist median-ulnar sensory latency difference.

**Table 2 T2:** Patient visits in the trial, data collection and outcome measures

	Pre-screen	Baseline	5 wk +5 d	10 wk ± 7 d	12 wk^† ^± 7 d	24 wk ± 7 d	52 wk ± 7 d
Diagnosis, inclusion & exclusion criteria	X						
Demographics		X					
Randomization		X					
Physical examination*		X		X		X	X
Nerve conduction testing		X					X
Outcome questionnaires		X	X	X		X	X
Rate of surgery					X	X	X
Sick-leave report		X	X	X		X	X
Adverse events		X	X	X		X	
Study medication		X					
Concomitant medication		X	X	X		X	

*Two-point discrimination, monofilament test, grip and pinch strength

^†^Surgery in participants choosing to have surgery

At baseline and at three follow-up occasions a physical examination is performed by the same physical therapist with extensive experience in hand therapy. Semmes-Weinstein monofilament and two-point discrimination tests of sensation are performed on the radial and ulnar aspects of each finger; two-point discrimination testing starts with a distance of 4 mm that is successively increased by 2 mm until the correct tactile discrimination is recorded. Grip strength and 3-point pinch strength are measured with the Baseline dynamometer and pinch gauge (Chattanooga Group, Hixson, Tennessee, USA), respectively (three trials for each hand). Before examination, the patients are instructed not to discuss their treatment with the assessor and will have their palms covered with a dressing to conceal possible scar after carpal tunnel release. The assessor is thus blinded to whether the patient had or had not undergone surgery after the injection. At the 10-week examination the success of blinding is evaluated by asking the examiner and patient to record whether they think the patient had received active treatment. After the 52-week physical examination the patient will proceed to nerve conduction testing keeping the same palm dressing so that the examiner also will be blinded.

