### Follow-up

At the *Baseline *visit, demographics, earlier and ongoing disease, and concomitant medication are recorded. The baseline data include weight, height, and smoking and employment status. The patient completes a questionnaire that includes demographic data, the CTS symptoms severity scale, the 11-item disabilities of the arm, shoulder and hand (*Quick*DASH) questionnaire, and the SF-6D. A physical examination is performed.

At *5 weeks *after injection a telephone interview is conducted by the investigator and the patient is asked to complete the CTS symptoms severity scale and concomitant medication and adverse events (AEs) will be recorded.

At *10 weeks *after injection the patient is examined by the physical therapist. The investigator asks the patient whether she/he wants to proceed with surgery as planned at 12 weeks after injection or whether the patient has experienced adequate symptom relief that she/he wants to continue follow-up and not have the planned surgery at this stage. An evaluation similar to the baseline evaluation is performed and the indication for surgery is recorded. The patient completes the CTS symptoms severity scale. Concomitant medication and AEs are recorded. Possible use of a wrist splint since the injection and its frequency is recorded.

At 12 weeks the patient who had chosen to have surgery is operated on as scheduled.

At *24 weeks *after injection the patient is examined and asked to complete a questionnaire including the CTS symptoms severity scale, *Quick*DASH, and the SF-6D as well as to rate satisfaction with the treatment on a visual analog scale from 0 (very dissatisfied) to 100 (completely satisfied). Concomitant medication and AEs are recorded.

At *52 weeks *after injection the patient is asked to attend a physical examination and nerve conduction tests and complete the questionnaires.

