### Primary endpoint

1. The CTS symptom severity score change at 10 weeks after treatment:

1) 80 mg Methylprednisolone vs. placebo

2) 40 mg Methylprednisolone vs. placebo

3) 80 mg Methylprednisolone vs. 40 mg Methylprednisolone

2. The rate of surgery at (in rank order) 52 weeks, 24 weeks, and 12 weeks after treatment:

1) 80 mg Methylprednisolone vs. placebo

2) 40 mg Methylprednisolone vs. placebo

3) 80 mg Methylprednisolone vs. 40 mg Methylprednisolone

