Analysis of the secondary end-points will be done with mixed models adjusting for baseline variables. We will also calculate the effect size for the symptom and function scales [20]. The AEs will be reported in table form and stratified in 4 groups according to severity; statistical comparison will be done when appropriate. When at least 60 patients have completed the 24-week visit the frequency of SAEs and of AEs with persistent symptoms will be calculated and the results will be reported and discussed with the Swedish Medical Products Agency.

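### Adverse event recording ends at 24 weeks while surgery is counted to 52, so AEs of later operations, late-onset AEs and the outcome of AEs open at week 24 are not recorded as AEs

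*Protocol article*

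**What the plan says.** The article fixes the AE window at 24 weeks and does so consistently.

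- Outcome Measures: "All AEs are recorded during 24 weeks".
- Evaluations, Table 2: the row "Adverse events" is marked at baseline, 5, 10 and 24 weeks and is blank at 52 weeks.
- Follow-up: at the 24-week visit, "Concomitant medication and AEs are recorded". At 52 weeks, "the patient is asked to attend a physical examination and nerve conduction tests and complete the questionnaires"; AEs are not listed.
- Discussion: the stated safety aim is a comparison of injection with placebo over the first 24 weeks.

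The surgery endpoint runs longer. Primary endpoint 2 is "The rate of surgery at (in rank order) 52 weeks, 24 weeks, and 12 weeks after treatment". Surgery for those who choose it is scheduled at 12 weeks, but Table 2 counts surgery again at 24 and 52 weeks, and time to surgery is a secondary endpoint. For safety review, Statistical Analysis plans that once at least 60 patients have completed the 24-week visit, "the frequency of SAEs and of AEs with persistent symptoms will be calculated".

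**The concern.** The Background justifies the trial partly by the harms of surgery. It says of postoperative pain and weakness that "These are common problems and may last several months after surgery", and it also names infection, a chronic pain syndrome and nerve damage. Avoided surgery is then counted over a full year, whereas AEs, including those of surgery, are recorded for less than half of it.

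The gap need not be balanced between arms. The Background itself treats delay of surgery as a cost of an ineffective injection. If steroid relieves symptoms for some months and then wears off, placebo patients would tend to be operated on at week 12, inside the AE window, and steroid patients later, with less AE coverage or none. The AE table would then look better for steroid partly because its operations came later. At stake is whether the 52-week surgery result can be set beside an AE comparison over the same period.

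**Working it through.** The plan gives no derived figure on this point. The check compares stated weeks, and the sample size is unaffected.

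Inputs:
- End of AE recording: week 24, visit window ± 7 days (Outcome Measures; Table 2).
- Planned surgery: week 12, ± 7 days (Follow-up; Table 2).
- End of surgery counting and last visit: week 52 (Primary endpoint; Table 2).

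1. Time without AE recording: 52 − 24 = 28 weeks; 28/52 = 54% of follow-up.

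2. Postoperative AE coverage for an operation at week s is max(0, 24 − s) weeks.
   - s = 12: 24 − 12 = 12 weeks. With the windows, the shortest is (24 − 1) − (12 + 1) = 10 and the longest is (24 + 1) − (12 − 1) = 14.
   - As a share of postoperative time to week 52: 12/(52 − 12) = 12/40 = 30%.
   - s = 18, for illustration: 24 − 18 = 6 weeks.
   - s = 24 or later: 0 weeks, although the operation counts in the 52-week rate.

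3. Consequence by arm. Coverage per operation falls one week for each week that surgery is postponed, down to zero at week 24. An arm whose operations come later on average, between weeks 12 and 24 or beyond, therefore has less AE coverage per operation. The direction is clear if steroid postpones surgery. The size depends on the distribution of operation times, which the documents do not give, so no number of missed events is calculated.

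4. With recording to week 52, coverage is 52 − s: 40 weeks for surgery at week 12 and 28 weeks for surgery at week 24. Coverage per operation still differs with timing, but AEs and surgery are then counted over the same 52 weeks in every randomized group.

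**The case against.** The strongest reply is that the window is a stated scope. The drug is given once, at baseline. Carpal tunnel release is not randomized, no objective is to estimate its harms, and the safety aim is limited to the first 24 weeks. All of this stands: nothing is contradicted, and the 24-week AE comparison is valid for what it claims. It does not supply AEs for the period after week 24 in which surgery is still being counted.

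Several stronger readings are tempting, and the documents do not support them.

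- A reader might infer that persistent AEs are not counted at all. Events that start by week 24 are recorded, and the planned safety review counts those with persistent symptoms. What is missing is their later course.
- A reader might infer that late harm cannot be seen. The 52-week visit collects symptom, function and utility scores, sensation, grip and pinch strength, nerve conduction and sick leave. Lasting harm could show there between groups, though not as an event with a cause and severity; an infection that had healed need leave no trace.
- A reader might infer that nerve deterioration is lost because of "At baseline and the last follow-up (Table 2) median nerve conduction testing of both hands is performed". The 52-week test is itself recorded as data, so relabelling a worsening as an AE would add nothing.
- A reader might want a count of operations without AE coverage. The documents give no basis for one, and the planned operations at week 12 are covered for about 10 to 14 weeks.

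An article also condenses the full protocol, which may provide for following open or serious events to resolution. That cannot be excluded here. The 24-week cut-off itself, however, is stated outright and repeated, so it is not an omission of the article.

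**Conclusion.** The point holds as a limitation of a deliberate design choice. As the article stands, AEs of operations after the 24-week visit, AEs that start after week 24, and the outcome of AEs open at week 24 are not recorded as AEs, although patients are seen at 52 weeks and surgery is a primary endpoint to that time.

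The certain part is the timing: 28 of 52 weeks without AE recording, about 12 weeks of postoperative coverage for surgery at week 12, and none after the 24-week visit. The differential loss between arms is conditional on steroid mainly postponing surgery, and its size is unknown. The verdict assumes that the full protocol, not shown, does not extend AE follow-up beyond what the article states. The efficacy analyses and the 24-week safety comparison are not affected.

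**What to change.** Mark adverse events at 52 weeks in Table 2 and extend the recording period in Outcome Measures to 52 weeks. At that visit, record (i) the outcome of each AE open at week 24 and (ii) any AE since then, including AEs of carpal tunnel surgery. Collect this on the 52-week questionnaire, or through whoever records surgery status and sick leave. Do not collect it through the physical therapist or the nerve conduction examiner, who must stay blind to whether the patient has been operated on. Report AEs by randomized group to 24 weeks as planned and additionally to 52 weeks.

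The cost is small: the visit already takes place and already collects surgery status, sick leave and questionnaires, so a few items are added without further procedures. The downside is recall over 28 weeks. Late minor events will be less complete than early ones, and the report should say so.

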### Blinding

The nurse at the outpatient clinic prepares the medication with a label covering the syringe. The injection will then be administered to the patient by the investigator. The placebo is clear and Methylprednisolone is a white suspension. In subfascial injections such as in the carpal canal leakage from the injection canal is small. The investigator administering the injection presses a medical dressing over the puncture site while withdrawing the needle; this will conceal the color in case of leakage. The decision whether or not to have surgery is done by the patient at 10 weeks and the patients are instructed to make that choice based on their symptoms and functional status at that time. At the 24-week and 52-week patient visits the palm is covered by a bandage with a dressing to blind the examining physical therapist as to whether the patient had undergone surgery after the injection. All follow-up evaluations are done by a physical therapist blinded to the group assignment.

### Sample Size

Based on previous studies of surgical outcome in patients with idiopathic CTS the mean improvement in the CTS symptom severity scale at 12 weeks after surgery is about 1.6 (on the 1 to 5 point scale). A mean improvement of less than 0.8 in the CTS symptom severity score cannot warrant recommending steroid injection as an effective alternative treatment. With 90% statistical power, 5% significance level, and two-sided statistical tests, and assuming a standard deviation of 1.0 for the CTS symptom severity score the study can detect a true difference of at least 0.8 point on the CTS symptom severity score between an intervention group and the placebo group when 102 patients have been randomized. The aim will be to enroll 120 patients in the study to account for potential incomplete follow-ups.

### Primary endpoint

1. The CTS symptom severity score change at 10 weeks after treatment:

1) 80 mg Methylprednisolone vs. placebo

2) 40 mg Methylprednisolone vs. placebo

3) 80 mg Methylprednisolone vs. 40 mg Methylprednisolone

2. The rate of surgery at (in rank order) 52 weeks, 24 weeks, and 12 weeks after treatment:

1) 80 mg Methylprednisolone vs. placebo

2) 40 mg Methylprednisolone vs. placebo

3) 80 mg Methylprednisolone vs. 40 mg Methylprednisolone

### Secondary endpoint

1. The CTS symptom severity score change at 52 weeks

2. Time to surgery

3. The *Quick*DASH score at 10 weeks and 52 weeks

4. The SF-6D score at 10 weeks and 52 weeks

5. Patient satisfaction with treatment at 10 weeks and 52 weeks

6. Duration of sick leave at 52 weeks (for employed patients)

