**Methods/Design:**

The study is a randomized double-blind placebo-controlled trial. Patients referred to one orthopedic department because of CTS are screened. Eligibility criteria are age 18 to 70 years, clinical diagnosis of primary idiopathic CTS and abnormal nerve conduction tests or clinical diagnosis made independently by two orthopedic surgeons, failed treatment with wrist splinting, symptom severity of such magnitude that the patient is willing to undergo surgery, no severe sensory loss or thenar muscle atrophy, and no previous steroid injection for CTS. A total of 120 patients will be randomized to injection of 80 mg Methylprednisolone, 40 mg Methylprednisolone, or normal saline, each also containing 10 mg Lidocaine. Evaluation at baseline and at 5, 10, 24 and 52 weeks after injection includes validated questionnaires (CTS symptom severity scale, *Quick*DASH and SF-6D), adverse events, physical examination by a blinded assessor, and nerve conduction tests. The primary outcome measures are change in the CTS symptom severity score at 10 weeks and the rate of surgery at 52 weeks. The secondary outcome measures are the score change in the CTS symptom severity scale at 52 weeks, time to surgery, and change in *Quick*DASH and SF-6D scores and patient satisfaction at 10 and 52 weeks. The primary analysis will be carried out using mixed model analysis of repeated measures.

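### Patient satisfaction is a secondary endpoint at 10 and 52 weeks, but the visit text schedules the satisfaction scale only at 24 weeks, and nothing schedules it at 10 weeks

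*Protocol article*

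**What the plan says.** Two places in the protocol article set the endpoint times, and they agree. The Secondary endpoint section has "Patient satisfaction with treatment at 10 weeks and 52 weeks" as its fifth item. The Methods/Design paragraph of the abstract has "patient satisfaction at 10 and 52 weeks".

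The Follow-up section says what is collected at each visit. Satisfaction appears once, under 24 weeks, where the patient completes the symptom scale, QuickDASH and SF-6D "as well as to rate satisfaction with the treatment on a visual analog scale" running from 0 to 100. Under 10 weeks the section says "An evaluation similar to the baseline evaluation is performed and the indication for surgery is recorded", and then "The patient completes the CTS symptoms severity scale. Concomitant medication and AEs are recorded". Under 52 weeks the patient completes questionnaires that are not listed.

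Table 2 (Evaluations section) has one row for outcome questionnaires, marked at baseline and at 5, 10, 24 and 52 weeks. It does not break the row down by instrument and has no row for satisfaction. The Outcome Measures section describes the symptom scale, QuickDASH and SF-6D, but no satisfaction scale.

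**The concern.** The one visit with a named satisfaction rating is not an endpoint time, and neither endpoint time has a named rating. This goes beyond brevity. The article gives the instrument, its range and its visit, and the visit it gives does not match the endpoint list.

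What is at stake is the 10-week rating. At 10 weeks the patient decides about surgery, and those who choose it are operated on at 12 weeks. The 10-week rating is therefore the only satisfaction endpoint before the planned operation. In operated patients, a later rating of treatment may reflect both the injection and the surgery. Satisfaction is a judgement made at the time, so a 10-week rating that is not taken cannot be reconstructed, and the 24-week rating does not replace it.

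**Working it through.** No figure in the plan depends on this point. The 102 and 120 patients in the Sample Size section come from the symptom severity score alone. The check is therefore to set the passages side by side.

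| Visit | Instruments named in the Follow-up text | Table 2, outcome questionnaires | Satisfaction endpoint? |
|---|---|---|---|
| Baseline | Symptom scale, QuickDASH, SF-6D (with demographics) | Marked | No |
| 5 weeks | Symptom scale, by telephone | Marked | No |
| 10 weeks | Symptom scale, plus a baseline-like evaluation | Marked | **Yes** |
| 24 weeks | Symptom scale, QuickDASH, SF-6D, **satisfaction scale** | Marked | No |
| 52 weeks | Questionnaires, not itemised | Marked | **Yes** |

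Four pieces of wording might supply a satisfaction rating at an endpoint time.

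1. **The baseline-like evaluation at 10 weeks.** The baseline questionnaire is itemised and has no satisfaction item. It could not have one, because no treatment has yet been given. A visit modelled on baseline therefore does not bring satisfaction in. It does not exclude it either; it is simply no source for it.

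2. **The Table 2 row.** It is marked at 10 weeks, but also at baseline, where satisfaction with treatment cannot be asked, and at 5 weeks, where the visit text names only the symptom scale. A mark does not show which instruments are given, so the mark at 10 weeks does not establish a satisfaction rating. It does leave room for one to have been intended.

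3. **The abstract's list of questionnaires for all evaluations.** It names the symptom scale, QuickDASH and SF-6D. Satisfaction is not among them, although the same paragraph lists it as an outcome at 10 and 52 weeks.

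4. **The un-itemised questionnaires at 52 weeks.** This follows directly on the 24-week list, which includes satisfaction, so it may reasonably be read as covering it. The gap at 52 weeks is not firm.

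Timing relative to surgery: 10 weeks is 12 − 10 = 2 weeks before the scheduled operation. The 24-week rating comes 24 − 12 = 12 weeks after it, and the 52-week rating 52 − 12 = 40 weeks after it. Allowing for the visit windows in Table 2 (7 days either way at both 10 and 12 weeks), the latest 10-week visit is day 70 + 7 = 77 and the earliest surgery is day 84 − 7 = 77. Within these windows, the 10-week visit does not fall after the day of planned surgery.

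**The case against.** The strongest reply is that this is a journal article. Lists of instruments by visit usually sit in the full protocol or the case report form, which are not shown. The endpoint times are stated twice and consistently, so the intention to measure satisfaction at 10 weeks is clear. The 10-week text is silent on satisfaction rather than excluding it, and the generic Table 2 row could hold it.

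Much of this is fair, and it limits how far the point goes. It does not remove the mismatch: the article specifies the satisfaction scale at a visit with no satisfaction endpoint, and nowhere at 10 weeks.

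Three stronger readings are tempting, and the document does not support them.

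- A reader might infer that QuickDASH and SF-6D are also lost at 10 weeks, because "The patient completes the CTS symptoms severity scale" is the only instrument named there. That does not follow. The abstract lists both scales for the 10-week evaluation, the baseline-like evaluation would include them, and Table 2 is marked. Nothing gives the visit text priority over these.
- A reader might infer that no patient at all will have a 10-week satisfaction rating. That is too firm. The un-itemised row leaves open that the rating was intended and appears on the actual form.
- A reader might infer that the plan must separate satisfaction with the injection from satisfaction with surgery. The endpoint is satisfaction with treatment, and nothing in the document requires a split. That would be a preference.

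**Conclusion.** The mismatch between endpoint and schedule is real. It is firm for satisfaction at 10 weeks and open at 52 weeks. If sites follow the visit text and Table 2 as written, the 10-week rating is not collected, and with it goes the only satisfaction endpoint before planned surgery.

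The reach is limited to one of six secondary endpoints, at one of its two times. The primary endpoints, their analyses and the sample size are unaffected. The conclusion assumes that the article reflects what sites are told to collect. If the full protocol or the case report form already has the scale at 10 weeks, only the article's wording needs correcting.

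**What to change.** Reconcile the Follow-up section, Table 2 and the Secondary endpoint section. Name the satisfaction visual analog scale explicitly at the 10-week and 52-week visits in the Follow-up text, and show it at those visits in Table 2, in its own row or by itemising the outcome-questionnaires row. The 24-week rating can stay as it is.

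Check the case report form for the 10-week visit at the same time, since data not collected there cannot be recovered. The cost is a minor wording amendment and one extra item for the patient at visits already scheduled.
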